Participants will be required to complete the programme 5 days per week over 9 weeks. They will be encouraged to complete the programme in one session per day, but if required due to fatigue and/or scheduling issues, may complete the session in multiple bouts within a 24-hour period. Participants will be required to wear the equipment when performing the prescribed exercises. At the end of the study, a subset of participants will be invited to participate in a semistructured exit interview to discuss their experience using the TeleRehaB DSS system. This qualitative feedback on acceptability and usability will help to inform future iterations of the platform, for a larger-scale RCT and eventual adoption into local healthcare systems.

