#### Secondary outcome measures

Various secondary outcome measures will be used to assess clinical outcomes, programme effectiveness, system performance, AI model predictive power, e-health literacy and user experience. Please see table 2 for the detailed schedule of assessments.

**Table 2 T2:** Schedule of assessments for all participants enrolled in the TeleRehaB DSS study

		Screening	Baseline	Week 0	Weekly	Weeks 3 and 6	Post-intervention (week 10)	Monthly
Recruitment procedures	PIS informed consent	X	X					
Data collection and outcome measures	Demographics		X					
	HADS	X					X	
	DHI	X					X	
	FGA	X					X	
	MoCA	X					X	
	EQ-5D-5L		X				X	
	RAPA		X				X	
	ABC		X				X	
	Mini-BESTest		X				X	
	SVV		X				X	
	WEMWBS		X				X	
	FSS		X				X	
	SVQ		X				X	
	Exit interviews						X	
User experience measures	SUS						X	
	UEQ						X	
eHealth literacy measures	eHEALS		X					
	STAM-14		X					
	MDPQ-s		X					
Home-based interactions	Equipment installation and practice session (*IG only*)			X				
	Equipment de-installation (*IG only*)						X	
	Telephone call				X			
	Remote programme review					X		
	Perform HEP				X			
	Submit falls diary				X			X
	Submit exercise log				X			

ABC, Activities Specific Balance Confidence Scale; DHI, Dizziness Handicap Inventory; eHEALS, eHealth Literacy Assessment; EQ-5D-5L, EuroQol five-dimensional descriptive system; FGA, Functional Gait Assessment; FSS, Fatigue Severity Scale; HADS, Hospital Anxiety and Depression Scale; HEP, home exercise programme; IG, intervention group; MDPQ-s, Mobile Device Proficiency Questionnaire - short; Mini-BESTest, Mini-Balance Evaluation Systems Test; MoCA, Montreal Cognitive Assessment; PIS, Participant Information Sheet; RAPA, Rapid Assessment of Physical Activity; STAM, Senior Technology Acceptance and Adoption Model-14; SUS, System Usability Scale; SVQ, Situational Vertigo Questionnaire; SVV, Subjective Visual Verticality; TeleRehaB DSS, TeleRehabilitation Decision Support System; UEQ, User Experience Questionnaire; WEMWBS, The Warwick-Edinburgh Mental Wellbeing Scale.

Cost-effectiveness by means of the incremental cost-effectiveness ratio (ICER; the difference in mean costs divided by the difference in mean QALYs at the time of recruitment to the study and 1 year before the study and 1 year after the end of the intervention).

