#### Quality-adjusted life years

Health-related QOL will be assessed using the EQ-5D-5L at baseline and post-intervention, with utility values derived from country-specific tariffs. The area under the curve method will estimate QALYs over the intervention period, reflecting the intervention’s impact on participants’ quality and quantity of life.

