#### Cost-effectiveness analysis (incremental cost-effectiveness ratio)

Total costs for the intervention and control groups will be calculated by summing the following: (1) intervention-specific costs (ie, equipment, technology and software costs); (2) standard care costs (printing and distribution costs of OTAGO HEP and Meniere’s Dizziness booklet, estimated therapist time and healthcare facility usage for standard care participants); and (3) indirect costs of data utilisation of healthcare records 1 year post-intervention to capture primary care services and hospital usage. The *ICER* will be calculated as follows:

$$ICER=\frac{\Delta Cost}{\Delta QALYs}$$

where ΔCost is the difference in average costs between the intervention and control groups, and QALYs is the difference in QALYs gained. To assess the robustness of the ICER, a one-way sensitivity analysis will vary key inputs, such as utility values, cost assumptions and healthcare utilisation rates, to evaluate their impact on the ICER. This will help identify variables with the greatest impact on cost-effectiveness.

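### The dated healthcare-use window in the cost sum opens when the intervention ends, so care used during the 9–10 intervention weeks is not clearly in ΔCost for the TeleRehaB arms

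*Protocol article*

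**What the plan says.** The section on cost-effectiveness analysis builds total cost for the intervention and control groups from three items.

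1. "intervention-specific costs (ie, equipment, technology and software costs"). No healthcare use is named.
2. Standard care costs: printing and distributing the control materials, plus "estimated therapist time and healthcare facility usage for standard care participants". No dates are given.
3. "indirect costs of data utilisation of healthcare records 1 year post-intervention to capture primary care services and hospital usage". This is the only dated healthcare-use item in the sum.

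Under Secondary outcome measures, the ICER is framed "at the time of recruitment to the study and 1 year before the study and 1 year after the end of the intervention".

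The section on quality-adjusted life years says: "The area under the curve method will estimate QALYs over the intervention period". The Intervention section fixes the length of that period: "Participants will be required to complete the programme 5 days per week over 9 weeks". The Outcome measures section places the two site assessments at week 0 and week 10.

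**The concern.** The participants are at risk of falls and exercise at home on most days of the week. The protocol monitors falls and adverse events during this time, with weekly falls diaries and adverse event forms, but nowhere links those events to costs. Suppose a TeleRehaB participant falls in week 4 and attends an emergency department. Item 1 holds only equipment, technology and software. Item 2 is confined to standard care participants. Item 3, read plainly, starts after the intervention. That attendance has no clear place in ΔCost. The same attendance by a control might enter under item 2.

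The resulting ICER is to be compared with willingness-to-pay thresholds, with £20 000–£30 000 per QALY given as the UK example, to judge whether the system is a cost-effective alternative. The analysis plan is also being tried out for a future trial, so a gap in the cost window could carry over into that trial.

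This is separate from the question of costs and QALYs having different horizons. Extending QALY measurement to one year would still leave the intervention weeks without a dated healthcare-use cost.

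**Working it through.** The document states no figure for this point that could be reproduced. The check compares time windows and then looks at what each reading does to ΔCost.

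**Inputs**
- Programme length: 9 weeks (Intervention section).
- EQ-5D-5L assessments: baseline (week 0) and week 10 (Outcome measures, Table 2).
- Records window: 1 year post-intervention (cost-effectiveness section).
- One year = 365.25/7 = 52.18 weeks.
- The window opens at week 9 (programme end) or week 10 (post-intervention visit). The text does not say which.

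**Length of the gap**

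Share = gap / (gap + 52.18).
- Opens at week 9: 9 / 61.18 = 14.7%.
- Opens at week 10: 10 / 62.18 = 16.1%.

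**Overlap with the 10 weeks between EQ-5D-5L assessments**
- Opens at week 9: 1 week shared, 9 of 10 uncovered.
- Opens at week 10: none shared, 10 of 10 uncovered.

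**Effect on ΔCost by reading**

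Let H_I and H_C be mean healthcare cost per participant during the intervention weeks in the intervention and control groups. The full cost difference contains H_I − H_C.

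- *Window starts at the end of the intervention; facility use means in-trial care.* If item 2 captures all of H_C, the sum contains 0 − H_C. The error is (0 − H_C) − (H_I − H_C) = −H_I. ΔCost is too low, which favours the intervention.
- *Window starts at the end of the intervention; facility use means the cost of delivering the control programme.* In-trial care is missing from both groups. The error is 0 − (H_I − H_C) = H_C − H_I, whose sign is unknown. Separately, a delivery cost is charged to controls with no matching line in the TeleRehaB arms.
- *Records drawn at one year and reaching back to randomisation.* Item 3 covers the gap. If facility use also means in-trial care, control hospital use during the intervention could be counted twice.

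The document gives no event rates and no unit costs, so H_I and H_C cannot be given values.

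**The case against.** The strongest reply is that the wording is ambiguous and excludes nothing outright. The phrase about records could describe an extraction made at one year that looks back over the intervention, and no start date is given. The ICER sentence also names the time of recruitment, and its time points follow the reference to mean QALYs; it does not call them windows of healthcare use. The year before the study does not appear in the cost sum at all. All of this stands, and it is why the point is put as care that is not clearly included. It does not remove the point. The other statement, "1 year before the study and 1 year after the end of the intervention", reads most naturally as a period that begins when the intervention ends, and neither section names the intervention weeks.

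A reader might go further in four ways that the document does not support.
- *That in-trial care is never costed.* The undated control item may capture some of it for controls, and the look-back reading cannot be ruled out.
- *That the bias is known to favour the intervention.* Facility use is listed beside printing, distribution and therapist time, so it may well be a delivery cost. The direction is then open.
- *That most of the relevant care falls in these weeks.* No event timing or rates are given, and falls diaries continue for up to 6 months afterwards.
- *That Table 2 proves the omission because it schedules no resource-use form.* Records need no visit, and Table 2 does not list the planned post-intervention extraction either.

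It is also fair that the ICER sits among the secondary outcomes of a feasibility study that is not powered for effectiveness, and that an article may leave extraction details to a fuller document. That limits the weight of the point. The cost items and the window are nevertheless stated here, and the objection is to what they fix.

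**Conclusion.** The point holds in a limited form. On the plain reading, the dated healthcare-use window leaves out 9 to 10 weeks, or 14.7% to 16.1% of the span from baseline to one year post-intervention. Those weeks are nearly all of the period over which QALYs are estimated (9 or 10 of 10 weeks). For the TeleRehaB arms no other cost item clearly covers care used in that time. The facility-use item applies to controls only and needs defining on either reading: as in-trial care it would bias ΔCost towards the intervention, and as a delivery cost it has no intervention counterpart.

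This rests on two assumptions: that the post-intervention year starts at the end of the programme or at the week 10 visit, and that the three listed cost items are the whole sum. The overall direction and the monetary size cannot be derived from the document. The point is worth correcting because the ICER is meant to support a cost-effectiveness judgement and the correction is cheap.

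**What to change.** - State one records window for all three arms: from randomisation to one year post-intervention, with the calendar anchor for the end of the intervention given (week 9 or week 10).
- Sum the same primary care and hospital items over that whole span for every arm.
- Define healthcare facility use as either in-trial care or delivery cost, and apply it to all arms. Deleting it could remove a real control delivery cost. If it means in-trial care, make sure the records do not count it a second time.
- Use any data from the year before the study only as a baseline-cost covariate, not in ΔCost.

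Cost: a change of wording, a wider date range in an extraction already planned, and slightly more data handling. No new visit or participant form is needed.

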#### Sample size

The target sample size across all sites is 460. This equates to 60–100 participants per clinical site, with 30–50 participants recruited to intervention group (IG) and CG study arms, per clinical site, in line with recommendations for pilot feasibility studies.^49 52 53^

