#### Statistical approach for quality-adjusted life year and cost-effectiveness analysis

A mixed-effects regression model will compare QALYs and costs between groups, adjusting for confounders like age, baseline health and site. Cost-effectiveness will be evaluated against willingness-to-pay thresholds (eg, £20 000–£30 000 per QALY in the UK) to determine if TeleRehaB DSS is a cost-effective alternative to standard care.

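### The ICER is defined as a ratio of differences in group means with no adjustment stated, so read literally its QALY term carries chance baseline EQ-5D-5L imbalance; the link to the planned adjusted model should be written down

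*Protocol article*

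**What the plan says.** Four statements in the Protocol article bear on this.

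- *Quality-adjusted life years*: two utility measurements, since "Health-related QOL will be assessed using the EQ-5D-5L at baseline and post-intervention". The method follows: "The area under the curve method will estimate QALYs over the intervention period".
- *Cost-effectiveness analysis (incremental cost-effectiveness ratio)*: the formula ΔCost/ΔQALYs is printed, and its cost term "is the difference in average costs between the intervention and control groups, and QALYs is the difference in QALYs gained".
- *Secondary outcome measures*: the ICER is defined again as "the difference in mean costs divided by the difference in mean QALYs". The time frames attached to that definition are a separate matter and are not used here.
- *Statistical approach for quality-adjusted life year and cost-effectiveness analysis*: this section opens with the planned group comparison, worded as "A mixed-effects regression model will compare QALYs and costs between groups, adjusting for confounders like age, baseline health and site". The next sentence compares cost-effectiveness with willingness-to-pay thresholds.

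No sentence says that the model's estimates are the increments in the formula. None says that the formula excludes them. Baseline health is not tied to a particular instrument.

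**The concern.** With utility measured only at baseline and week 10, the area under the curve is the average of the two values multiplied by the time between them. The baseline value, which treatment cannot have influenced, therefore makes up half of each participant's QALY. If the ratio is taken from group means as its two definitions are worded, half of any chance baseline difference is booked as a QALY difference between the groups.

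The true QALY difference over about ten weeks is bound to be small, so a modest imbalance can shrink, inflate or reverse the denominator. A ratio with the wrong sign in its denominator cannot sensibly be set against the thresholds the article names. It could also disagree with the adjusted QALY comparison reported beside it. The article says its analysis plan is being tried out for a later trial, so an ambiguous estimator could be carried forward.

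**Working it through.** **Inputs from the article.** EQ-5D-5L is taken at week 0 and week 10, with an intervention period of 9 weeks, so T = 10/52 year (9/52 changes the QALY scale but not the probabilities below). The stated MCID range for utility is 0.03 to 0.52; the low end, 0.03, is used as the true gain d. On numbers, "The target sample size across all sites is 460", with "30–50 participants recruited to intervention group (IG) and CG study arms, per clinical site".

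**The plan's own figure.** Five sites × 60–100 gives 300–500 in total, and five × 30–50 gives 150–250 per group. The target of 460 lies inside the first range but is not derived. The equal ranges for the two groups are read as about 1:1, so n = 460/2 = 230 per group. The article gives no QALY, cost or ICER figure to reproduce.

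**Assumptions not in the article.** Utility SD 0.15–0.25 and correlation ρ between baseline and week 10 of 0.5–0.7. A sensitivity case assumes 20% loss: 0.8 × 230 = 184 per group.

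**Formulas.**
- QALY = T(u0 + u10)/2, so the true difference is Td/2 = (10/52)(0.03)/2 = 0.0029 (0.0026 with T = 9/52).
- SE of the unadjusted difference = (T/2)·SD·√(2(1+ρ))·√(2/n).
- SE adjusted for baseline utility = (T/2)·SD·√(1−ρ²)·√(2/n).
- Variance ratio = 2(1+ρ)/(1−ρ²) = 2/(1−ρ): 4.0 at ρ = 0.5 and 6.7 at ρ = 0.7, whatever the SD or n.
- Chance of a negative QALY difference = Φ(−(Td/2)/SE).

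**Results, n = 230 per group, d = 0.03, T = 10/52.**

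| SD | ρ | SE unadjusted | SE adjusted | Negative, unadjusted | Negative, adjusted |
|---|---|---|---|---|---|
| 0.15 | 0.5 | 0.00233 | 0.00116 | 10.8% | 0.7% |
| 0.15 | 0.7 | 0.00248 | 0.00096 | 12.2% | 0.1% |
| 0.20 | 0.5 | 0.00311 | 0.00155 | 17.7% | 3.2% |
| 0.20 | 0.7 | 0.00331 | 0.00128 | 19.2% | 1.2% |
| 0.25 | 0.5 | 0.00388 | 0.00194 | 22.9% | 6.9% |
| 0.25 | 0.7 | 0.00413 | 0.00160 | 24.3% | 3.6% |

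With 184 per group the ranges are 13–27% unadjusted and 0.4–9% adjusted. With d = 0.05 and 230 per group they are 2–12% unadjusted and below 1% adjusted.

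**How much imbalance is needed.** Given a baseline difference b, the expected unadjusted difference is (T/2)[d + (1+ρ)b]. It reaches zero at b = −0.03/1.5 = −0.020 (ρ = 0.5) or −0.03/1.7 = −0.018 (ρ = 0.7). With SD 0.20 the SE of b is 0.20·√(2/230) = 0.019, so a deficit that large in the intervention group has probability of about 14–17% (8–22% over SD 0.15–0.25).

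**Illustration.** Intervention mean utility goes from 0.70 to 0.75; control stays at 0.73.
- Area under the curve, unadjusted: (0.725 − 0.73) × 10/52 = −0.00096 QALY.
- Adjusted for baseline: (0.02 + 0.03ρ)/2 × 10/52 = +0.0034 (ρ = 0.5) to +0.0039 (ρ = 0.7).
- Net of baseline, another possible sense of QALYs gained: 0.05/2 × 10/52 = +0.0048.

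The same data give three denominators, one with the opposite sign.

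**The case against.** The strongest reply is that nothing is wrong, only unsaid. The formula section gives the standard definition of an ICER. That definition says what the ratio is, not how each increment is estimated, and a model-adjusted difference in means is still a difference in means. The next section is headed as the statistical approach for this very analysis, models the same two quantities, includes baseline health and leads straight into the thresholds. The abstract also mentions adjustment for site and relevant confounders. The covariate list is illustrative, and EQ-5D-5L is the natural measure of baseline health in a QALY model. A condensed article may leave such detail to a fuller plan, and the ICER is a secondary outcome of a feasibility study not powered for effectiveness.

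Most of this stands. A reader might infer that the plan commits to unadjusted differences, or that it contradicts itself by giving two answers for one quantity. The documents do not support that: neither section says the differences are unadjusted, and the model can be read as supplying the increments. Nor can the effect be put in pounds per QALY, because the article gives no cost difference. The illustration is also on the unfavourable side: with SD 0.20 and 230 per group, a deficit of 0.03 or more against the intervention has probability of about 5% (0.03/0.019 is about 1.6 SE).

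What does not fall away is that the article prints the formula and defines the ratio twice, both times without adjustment. Followed as written, that gives the noisier estimate. The planned one-way sensitivity analysis varies inputs such as utility values but does not correct a baseline difference between groups.

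**Conclusion.** The point holds as an ambiguity with a measurable consequence. The ICER is defined from differences in means with no adjustment stated, and the adjusted model is not said to feed it. Taken literally, the QALY difference has 4.0–6.7 times the variance of one adjusted for baseline utility. A true gain of 0.03 would appear as a QALY loss about 11–24% of the time, rather than about 0.1–7%.

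These figures rest on the assumed SD, correlation and 1:1 split, on the smallest effect in the article's MCID range, and on the literal reading. Larger true effects lower them. If the adjusted model already supplies the increments and baseline health already means baseline utility, the analysis is sound and only the wording needs to catch up.

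**What to change.** - In *Cost-effectiveness analysis* and *Secondary outcome measures*, state that the cost and QALY differences in the ICER are the adjusted group differences from the mixed-effects model.
- In *Statistical approach for quality-adjusted life year and cost-effectiveness analysis*, name each participant's baseline EQ-5D-5L utility as a covariate in the QALY model.
- Report any ratio of unadjusted means as descriptive only.

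The cost is a few phrases. Baseline EQ-5D-5L is already collected and the model is already planned, so no new data or visits are needed.

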## Methods

### Trial design

The study is a multicentre, assessor-blinded RCT, investigating the feasibility and acceptability of the TeleRehaB DSS in persons with stroke, MCI, vestibular dysfunction or long covid.^49^ All participants will be enrolled in a 9-week MBR home exercise programme (HEP), including individualised balance exercises (sitting, standing, walking), cognitive training and exergames (figure 1). All participants will be randomised into one of three study arms, where they will receive a HEP provided under the supervision of a clinician (physiotherapist or sports scientist): (1) the high-technology TeleRehaB DSS group (HT-IG), (2) the low-technology TeleRehaB DSS group (LT-IG) or (3) the control group (CG) standard of care HEP. No matter the study arm allocated, all participants will receive the same prescription pattern, receiving a weekly check-in call by a member of the research team, and remote programme reviews at weeks 3 and 6 by the treating clinician, to discuss exercise modifications, symptoms, falls and any technical problems.

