#### Randomisation and blinding

Participants’ will be randomised using an online platform (www.sealedenvelope.com), and opaque envelopes, into either the HT-IG, LT-IG or CG to undergo a HEP. Participants will not be able to choose their preferred group and must be willing to participate in the assigned group. Details of the randomisation procedure, eligibility screening and intervention procedure can be found in figure 3.

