### Intervention

#### Intervention group: TeleRehabilitation Decision Support System (high-tech and low-tech intervention arms)

Participants randomised into the TeleRehaB DSS IG will undergo a second randomisation into either the (1) high-tech group or (2) low-tech group.

The HT-IG will receive all components of the TeleRehaB DSS, consisting of a depth camera, lightweight AR headset that displays the hologram, inertial measurement unit (IMU) body-worn sensors, to record movement, a chest heart rate monitor and smartwatch for activity monitoring (figure 4). The AI-DSS will suggest multisensory balance exercises, including cognitive training and exergames delivered by AR. The platform also provides real-time feedback on individual’s performance based on collected IMU data, which are analysed using an EDGE computer processing unit. The LT-IG will receive a basic version of TeleRehaB DSS, with a depth camera, tablet and IMU sensor monitored exercises with real-time feedback, multisensory balance exercises and cognitive games, but without the exergames, smartwatch, mobile phone or AR.

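### The trial randomises two different TeleRehaB DSS versions, but the cost-effectiveness analysis fixes one pooled ICER and one threshold decision that cannot inform on either version

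*Protocol article*

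**What the plan says.** The Trial design section of the protocol article states: "All participants will be randomised into one of three study arms". Randomisation and blinding names the same three destinations: "into either the HT-IG, LT-IG or CG to undergo a HEP". The section on the intervention group describes two steps, with those allocated to TeleRehaB DSS who "will undergo a second randomisation into either the (1) high-tech group or (2) low-tech group". No allocation ratio is given for either step.

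That same section describes two different packages. HT-IG has the full system, including AR headset, smartwatch and exergames. LT-IG has a basic tablet version without those three items.

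The economic analysis has two groups. In the cost-effectiveness section, ΔCost "is the difference in average costs between the intervention and control groups", and equipment, technology and software are listed as the intervention-specific costs. The section on the statistical approach to QALYs and cost-effectiveness then compares groups in a mixed-effects model and judges TeleRehaB DSS once against a threshold (for the UK, £20,000 to £30,000 per QALY).

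The Sample size section also counts two groups: "This equates to 60–100 participants per clinical site, with 30–50 participants recruited to intervention group (IG) and CG study arms, per clinical site".

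**The concern.** The cost items named for the intervention are the ones on which HT and LT differ. Averaging over both arms gives the cost per QALY of a package that no participant receives and no health service would buy. The average moves with the share of intervention participants allocated to HT, even if nothing about either version changes. None of the inputs named for the one-way sensitivity analysis (utilities, costs, healthcare use) is that share.

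The trial is meant to supply preliminary data for a definitive trial. Three questions bear on what to take forward: whether LT is worth its cost over standard care, whether HT is, and whether HT is worth its added cost over LT. The pooled ICER answers none of them.

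**Working it through.** **1. The plan's own numbers.** Two groups of 30–50 give 2 × 30 = 60 and 2 × 50 = 100 per site, which matches the stated range. Five sites give 300–500, and 460 lies inside (460/5 = 92 per site, 46 per group). The sample size is consistent for IG against CG. A 1:1:1 allocation does not fit it: with at least 30 in CG, IG would need at least 60, above the stated 50. The first step is therefore near 1:1 by implication. The HT:LT ratio cannot be recovered.

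**2. The pooled ICER.** Let w be the HT share of the intervention group, and let C and Q be incremental cost and QALY gain against control. Then

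pooled ICER = [w·C_HT + (1 − w)·C_LT] / [w·Q_HT + (1 − w)·Q_LT].

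The protocol gives no costs or expected gains, so every input below is an assumption.

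| Assumed inputs | HT | LT | Pooled, w = 1/2 | Pooled, w = 1/3 to 2/3 | HT v LT |
|---|---|---|---|---|---|
| £1,500 and £500; 0.02 QALY each | £75,000 | £25,000 | £50,000 | £41,667 to £58,333 | HT dominated |
| £3,000 and £1,000; 0.05 QALY each | £60,000 | £20,000 | £40,000 | £33,333 to £46,667 | HT dominated |
| £1,500 and 0.05; £1,000 and 0.04 | £30,000 | £25,000 | £27,778 | £26,923 to £28,571 | £50,000 |

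In the third row the pooled figure is close to both arm-specific figures. It still hides that moving from LT to HT costs (1,500 − 1,000)/(0.05 − 0.04) = £50,000 per QALY.

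**3. When the decision changes.** Take £1,500, £500, w = 1/2 (pooled cost £1,000) and an equal gain Q. At £30,000 per QALY:

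- LT passes if Q ≥ 500/30,000 = 0.0167.
- The pooled figure passes if Q ≥ 1,000/30,000 = 0.0333.
- HT passes if Q ≥ 1,500/30,000 = 0.05.

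Between 0.0167 and 0.0333, pooling rejects an LT version that passes. Between 0.0333 and 0.05, it accepts an HT version that fails. Below 0.0167 all three fail, and above 0.05 all three pass. At £20,000 the three cut-points are 0.025, 0.05 and 0.075.

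**4. Precision by arm.** The 95% half-width in SD units is 1.96·√(1/n₁ + 1/n₂). If both steps are 1:1, CG/HT/LT are 230/115/115:

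- IG v CG (230, 230): 0.183
- HT or LT v CG (115, 230): 0.224
- HT v LT (115, 115): 0.258

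**The case against.** The strongest reply is that this is an unpowered feasibility study whose stated comparison is TeleRehaB DSS with standard care. HT against LT is not among its aims, and the pooled ICER is a legitimate estimate for the mix as randomised. All of that stands. A reader might call the pooled figure uninterpretable, but it is interpretable as an average and merely uninformative about each version.

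The illustration can also be challenged. If QALYs accrue only over the intervention period, as the QALY section says, then with linear change over 10 weeks the gain is ½ × (10/52) × the end-point utility difference. Gains of 0.0167 to 0.0333 then need a difference of about 0.17 to 0.35, and 0.05 needs about 0.52. The MCID range that the protocol cites is 0.03 to 0.52, so the affected band is possible but lies well above its lower end. The misclassification is conditional on inputs, not demonstrated.

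Two stronger readings are tempting and are not supported:

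- **That HT and LT have half their stated size.** The 30–50 applies to IG and CG. No HT or LT target is stated, so none is missed, and a half follows only if the second step is 1:1. No power is claimed, so none is lost.
- **That the clinical tests ignore the third arm because Mann-Whitney takes two samples.** The repeated-measures ANOVA accepts three groups, Mann-Whitney can be run pairwise, and the Statistical analysis section does not say how many levels its group factor has.

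The reply does not reach the ICER definition and the single threshold decision. These are written in the article itself, for two groups, and are not details left to an analysis plan.

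**Conclusion.** The point holds for the cost-effectiveness analysis. As written, it yields one ICER that depends on an unstated HT:LT mix and cannot say whether either version meets the threshold or whether HT justifies its cost over LT. The size depends on costs and effects that the protocol does not give. With a threefold cost difference and equal gains, the £30,000 verdict is wrong for one version whenever the gain lies between about 0.017 and 0.05 QALY. With closer inputs the pooled figure is nearly right for both. A reader might infer that the trial is undersized or that its clinical analysis is two-group by design. The text supports neither. This is an inexpensive improvement that should be made, not a fault that invalidates the trial.

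**What to change.** - **Economic sections.** Define the analysis by randomised arm and make it fully incremental across CG, LT and HT. Take costs and QALYs per arm from the mixed-effects model with a three-level arm factor, order the options by cost, exclude dominated ones, and report net monetary benefit with 95% CI at the chosen thresholds. Keep pooled IG against CG as a secondary result.
- **Statistical analysis.** Use the same three-level arm factor in the clinical outcome model. Report HT v CG and LT v CG, with HT v LT labelled exploratory.
- **Randomisation and Sample size.** State the ratio of both steps once and give the resulting number per arm. This is 230/115/115 for CG/HT/LT only if both steps are 1:1.

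No new data or participants are needed. The cost is a few added contrasts and wider intervals: under those splits, about ±0.22 SD for HT or LT against control and ±0.26 SD for HT against LT, compared with ±0.18 SD for the pooled contrast.
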